### Statistical analysis

Data analysis of the present RCT will be conducted on an intention to treat (ITT) participants. ITT means outcome data obtained from all participants are included in the data analysis, regardless of protocol adherence. The data will be checked for accuracy and completeness at random intervals. The data will be expressed as means ± SD. For each variable, the percentage change will be calculated, as follows: [(E–B)/B ×100]; *E* is the end value, and *B* is the baseline value of the variable.

The Kolmogorov-Smirnov test will be used to examine the normality of the data. The intervention arm (SB) will be compared against the control (placebo) for all primary and secondary outcomes. The paired sample *t*-test and independent sample *t*-test will be performed for the comparison of parametric variables within and between groups, respectively. For non-parametric variables, the Mann-Whitney test and Wilcoxon signed rank test will be applied. Confounding factors including baseline values will be controlled using the analysis of covariance (ANCOVA) test. IBM SPSS software (version 21) (Armonk, NY, USA) will be used to analyze the data. A *P*-value less than 0.05 will be considered a statistically significant.

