### Participants

The study will involve 50 obese individuals. Participants will be both male and female aged 18 to 60 years old, with body mass index (BMI) of 30 to 40 kg/m^2^; non-inclusion criteria will be included: lack of interest in continuing the study; having diabetes, kidney diseases, heart failure, rheumatic diseases, cancers, liver failure, gastrointestinal disorders; history of obesity surgery; following a weight loss diet or taking any supplements or weight loss drugs in the last 6 months; smoking; and pregnancy, lactation, or menopause.

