### Sample size

The sample size was estimated based on serum changes of GLP-1 [22], 95% confidence interval, and 80% power (two-sided *α* = 0.05 and *β* = 0.2) using sample size formula (Fig. 2) suggested for comparison of mean between the two groups when the endpoint is quantitative data in parallel designed RCTs. Furthermore, the means and standard deviation (SD) [23] of GLP-1 levels in the study mentioned above were as follows: Δμ = 17.84; SD1 = 17.93; and SD2 = 22.49. Lastly, considering a 20% dropout rate, 25 subjects were calculated for each group. Individuals who fulfilled the eligibility criteria will be included in the RCT.

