**Fig. 3 Fig3:**
[figure not shown]
SPIRIT figure: schedule for enrollment, intervention, and assessment

The research team will provide weekly communications via phone calls and messages to inform the participants about obesity, the current status of the study, and plans for the next phase, emphasizing study benefits as well as to acknowledge their support. In week 4, there will be a face-to-face session with the participant to assess anthropometric changes and help to maintain interest in study.

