### Criteria for discontinuing or modifying allocated intervention

Since SB may affect the composition of the gut microbiota, temporary gastrointestinal symptoms such as bloating or diarrhea may occur. Taking the recommended daily dose regularly, gastrointestinal tolerance improves, and the symptoms usually disappear. However, the trial medication should be withdrawn from subjects reporting gastro-intestinal intolerance. This should be reported as an adverse event.

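### The analysis labelled ITT is an available-case analysis of about 40 of 50 randomised participants, and week-4 data on a primary outcome go unused

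*Protocol article*

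**What the plan says.** All references are to the protocol article.

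- **Statistical analysis** declares an ITT analysis and defines it: "ITT means outcome data obtained from all participants are included in the data analysis, regardless of protocol adherence". Change is computed from an end and a baseline value. The tests named are paired and independent t-tests, Wilcoxon and Mann-Whitney tests, and ANCOVA adjusting for baseline.
- **Outcomes** makes anthropometric indices, GLP-1 and the expression of three genes primary. It sets baseline and day 60 as the time points for all outcomes and all participants, and refers to Fig. 3 (not shown) for the schedule.
- **Sample size** reaches 25 per group after "considering a 20% dropout rate".
- **Intervention**, in the text after the Fig. 3 caption, adds a visit: "In week 4, there will be a face-to-face session with the participant to assess anthropometric changes". No stated analysis uses it.
- **Criteria for discontinuing or modifying allocated intervention** says "the trial medication should be withdrawn from subjects reporting gastro-intestinal intolerance". It does not say whether those participants are still measured at day 60.

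**The concern.** The definition has two halves. Keeping participants regardless of adherence is right. Restricting the set to data that were obtained is the difficulty: someone randomised but not measured at day 60 is outside the analysis, and the label hides this. A reader of the trial report would take ITT to mean that all 50 randomised participants are accounted for.

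If the reasons for missing day 60 relate to treatment or response, the remaining participants are no longer two comparable randomised groups. For the anthropometric outcomes part of this is avoidable. A participant lost after week 4 already has a post-baseline measurement on a primary outcome, and the stated analyses discard it.

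**Working it through.** **1. Reproduce the planned size.** Inputs, all from Sample size: "Δμ = 17.84; SD1 = 17.93; and SD2 = 22.49", two-sided α = 0.05, power 80%, 20% dropout.

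- Common SD = √[(17.93² + 22.49²)/2] = √413.64 = 20.34.
- n per arm = 2 × (1.960 + 0.842)² × 20.34² / 17.84² = 20.40.
- With dropout: 20/(1 − 0.20) = 25. Other rounding conventions give 25 to 27 (20.40 × 1.2 = 24.5, so 25; 20.40/0.8 = 25.5, so 26; 21/0.8 = 26.25, so 27).

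The stated 25 per group reproduces, so the sample size is not in error. It also shows that the trial was sized to analyse about 20 per arm.

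**2. Who is analysed under the stated rule.** 25 × 0.80 = 20 per arm, or 40 of 50. Each named comparison of change needs an observed end value, so the other 10 contribute to none of them.

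**3. What retention is worth in precision.** GLP-1 power for the design difference:

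| Per arm | Normal approximation | t-test |
|---|---|---|
| 20 | 79.2% | 77.1% |
| 25 | 87.3% | 86.0% |

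**4. Illustration of bias.** Assume that a share p = 0.20 of one arm is lost, that the lost participants differ from the measured ones in that arm by g SD, and that losses in the other arm are random. The full-arm mean is then the measured mean plus p × g, so the observed difference is off by p × g. The planned effect is 17.84/20.34 = 0.877 SD.

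| g (assumed) | Shift, SD | GLP-1 units | Share of 17.84 |
|---|---|---|---|
| 0.25 | 0.05 | 1.0 | 6% |
| 0.50 | 0.10 | 2.0 | 11% |
| 1.00 | 0.20 | 4.1 | 23% |

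For scale, the standard error of the difference at 20 per arm is √(2/20) = 0.32 SD. Shifts of 0.10 and 0.20 SD are thus about 0.3 and 0.6 standard errors.

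**5. What week 4 can recover.** If k of the 10 lost participants leave after week 4, a repeated-measures model has post-baseline anthropometric data on 40 + k of 50. The article does not give the timing of loss, so k may lie anywhere from 0 to 10. GLP-1 and gene expression have only a baseline and an end sample, so for them week 4 recovers nothing.

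**The case against.** The strongest reply is that the article already protects most of what matters. Outcomes are to be evaluated at day 60 for all participants, data count regardless of adherence, and the discontinuation rule withdraws the capsules, not the person. Imputation and sensitivity analyses are commonly left to an analysis plan that is not shown, and t-tests or ANCOVA can be run on imputed data. The bias figures are assumed and small against the standard error. With one baseline and one end value, imputing GLP-1 from baseline alone under missing-at-random gives essentially the planned ANCOVA estimate.

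Much of this stands, and it rules out several stronger readings that a reader might infer:

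- *That this is a completer or per-protocol analysis.* It is not: participants who stop capsules stay in if measured.
- *That stopping capsules for intolerance means loss from the trial.* The text does not say so. The article is also not of one mind on how often intolerance would occur: the discontinuation section expects temporary symptoms, while Adverse effects, safety, and data monitoring says none are known at this dose.
- *That randomised participants are removed for "lack of interest in continuing the study".* Participants lists this as a non-inclusion criterion, and Blinding and randomization of participants has criteria checked before allocation. The phrase is awkward, but nothing shows it operating after randomisation.
- *That the 0.10 to 0.20 SD shift estimates actual bias.* It is arithmetic on assumed differences.

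Two things are not answered. The article does more than stay silent: it states a definition of ITT that describes an available-case set. And the week-4 values on a primary outcome are already to be collected, while Outcomes and Statistical analysis confine the analysis to baseline and day 60. Fig. 3 may list week 4, but that would not bring it into the stated tests.

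**Conclusion.** The point holds in this limited form. At the planned dropout, the analysis called ITT covers about 40 of 50 randomised participants and should be described as available-case. For the anthropometric primary outcomes, a better method is open at little cost, because an intermediate measurement is already scheduled. For GLP-1 and gene expression, the planned baseline-adjusted ANCOVA is reasonable; its weaknesses are the label and the lack of any check on departures from missing-at-random.

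The count of 40 rests on the 20% planning allowance, which is not an observed rate. The illustrated shift of 6% to 23% of the planned GLP-1 effect rests on assumed differences of 0.25 to 1.0 SD confined to one arm. The gain from week 4 depends on how many participants leave after that visit and on which indices are measured there; the text gives neither.

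**What to change.** 1. **Anthropometric outcomes.** Fit a mixed model for repeated measures to the week-4 and day-60 values, adjusted for baseline, with all randomised participants as allocated and day 60 as the target contrast. State which indices are measured at week 4.
2. **GLP-1 and gene expression.** Keep the baseline-adjusted ANCOVA, describe it as available-case, and add one delta-adjusted sensitivity analysis for missing day-60 values.
3. **Follow-up.** State explicitly that participants who stop capsules remain in follow-up to day 60, in line with the Outcomes section.
4. **Label.** Replace the ITT definition with one that separates analysis as allocated from the handling of missing end values.

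The cost is revised wording and modest analyst time. No new visit is needed, since week 4 and day 60 are already scheduled. The mixed model relies on a missing-at-random assumption, which should be stated with the result.

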### Outcomes

Primary outcomes will be changes in means of anthropometrics indices, serum levels of GLP1, and fold change of PGC-1α, PPARα, and UCP1 genes between the control and intervention groups. Secondary outcomes are to compare the changes in means of lipid profile (serum levels of TG, TC, HDL-C, and LDL-C), FBS, fasting plasma insulin level, HOMA-IR, ALT, AST, and ALP between the control and intervention groups. All primary and secondary outcomes will be evaluated at the baseline and the end of the study (day 60 after intervention) for all participants. All outcomes and time points are specified in Fig. 3.

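### Two competing between-group analyses are fixed for every outcome at P<0.05, and the plan does not say which one decides

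*Protocol article*

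**What the plan says.** All places are in the protocol article.

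- **Outcomes:** "Primary outcomes will be changes in means" of the anthropometric indices and GLP-1, and fold change of three genes, compared between the arms. The secondary outcomes are changes in means as well.
- **Statistical analysis, scale:** a second metric appears here: "For each variable, the percentage change will be calculated, as follows".
- **Statistical analysis, unadjusted tests:** "The Kolmogorov-Smirnov test will be used to examine the normality of the data". Depending on the result, paired and independent t-tests "will be performed for the comparison of parametric variables within and between groups, respectively", or the Wilcoxon signed rank and Mann-Whitney tests are used.
- **Statistical analysis, adjusted test:** an ANCOVA is to control confounders, of which only the baseline value is named.
- **Threshold:** a P "value less than 0.05 will be considered a statistically significant", with no distinction between analyses.
- **Blinding and randomization of participants:** allocation is stratified by two age groups and by gender. The Statistical analysis section names neither as a covariate.

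**The concern.** Each outcome can end with at least two between-group P values, one unadjusted and one from ANCOVA, and the text does not say which answers the trial question. This has two consequences. If the choice is made after the results are seen, the 5% error rate is not held. If the unadjusted test is chosen, the precision available from the baseline measurement is thrown away.

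Three features widen the choice: the trial data decide between a comparison of means and a rank test, the ANCOVA covariates are open, and the percentage-change and within-arm results have no stated status. The within-arm tests cannot isolate butyrate, because both arms are put on a hypo-caloric diet and a change over time is expected in each.

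**Working it through.** **Inputs from the Sample size section:** "Δμ = 17.84; SD1 = 17.93; and SD2 = 22.49"; two-sided 5% and 80% power; "considering a 20% dropout rate, 25 subjects were calculated for each group". **Assumed, not in the article:** the correlation ρ between baseline and end value, the coefficient of variation (CV) and the distribution.

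**1. The plan's own figure.** Sum of squared SDs: 17.93² + 22.49² = 321.5 + 505.8 = 827.3. Pooled SD = √(827.3/2) = 20.34. Per group, n = (1.96 + 0.84)² × 827.3 / 17.84² ≈ 20.4. Then 20/(1 − 0.20) = 25, so the planned size reproduces apart from rounding. About 20 per arm are expected to be evaluable.

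**2. Error rate when the better of two analyses is reported.** With no treatment effect, the change-score and ANCOVA test statistics have correlation √((1 + ρ)/2). The chance that at least one exceeds ±1.96 (bivariate normal) is:

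| ρ | correlation of the two tests | either significant |
|---|---|---|
| 0.3 | 0.806 | 7.8% |
| 0.5 | 0.866 | 7.3% |
| 0.8 | 0.949 | 6.5% |
| 0.9 | 0.975 | 6.0% |

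Simulation agrees. With 20 or 25 per arm, ρ 0.5 or 0.8, normal data with CV 0.15 or 0.30 or lognormal data with CV 0.5, and 3,000 trials per scenario:

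- ANCOVA alone: 4.3-5.6%.
- The test picked by Kolmogorov-Smirnov on change, alone: 4.6-5.6%.
- Either of these two: 6.2-8.0%.
- The same with percentage change also tested: 7.1-9.2%.

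A separate simulation of 4,000 trials with ρ 0.3-0.7 gave 6.7-8.6% for change or ANCOVA, and 7.7-9.8% with percentage change added.

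**3. Power for the planned GLP-1 effect, 20 per arm, ρ = 0.5.**

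- Change score: SD = 20.34 × √(2(1 − 0.5)) = 20.34. Noncentrality = 17.84/(20.34 × √(2/20)) = 2.77. On 38 degrees of freedom, power is 77%.
- ANCOVA: residual SD = 20.34 × √(1 − 0.5²) = 17.61. Noncentrality = 17.84/(17.61 × √(2/20)) = 3.20. On 37 degrees of freedom, power is about 88%. Simulation gives 86-87%, because the slope is estimated and chance baseline imbalance costs a little.

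The article leaves open whether the planning SDs are SDs of values or of changes. At ρ = 0.5 this makes no difference, since 2(1 − ρ) = 1.

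**4. Sensitivity to ρ.** The ratio of ANCOVA variance to change-score variance is (1 + ρ)/2: 0.75 at ρ = 0.5, 0.90 at 0.8 and 0.95 at 0.9. If the planning SDs are SDs of change, then at ρ = 0.9 the ANCOVA SD is 20.34 × √0.95 = 19.82, and power is 79% against 77%. If they are SDs of values, both powers exceed 99% at ρ = 0.9.

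**The case against.** The other side has several sound points.

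- **The efficient analysis is already listed.** This stands. ANCOVA with baseline needs to be designated, not introduced.
- **Ranking of analyses, covariates and transforms often sits in an SAP, and this is a condensed article.** This stands only in part. The article does more than stay silent: it fixes two between-group analyses and a data-driven gate, and an SAP that repeated the section would carry the same ambiguity.
- **The 6-9% is a worst case.** This stands. It supposes that the more favourable result is always the one reported, and the plan does not say so.

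A reader might infer more than the text supports:

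- *The normality pre-test itself inflates error.* It does not materially: taken alone it gives 4.6-5.6%. Its fault is that trial data choose between means and ranks when the Outcomes section asks about means.
- *Every outcome is tested on several scales, with 10-12% error.* Percentage change is only said to be calculated, in the sentences that describe the data. The 10-12% also needs a test of end values, which the plan does not state.
- *Percentage change is the least efficient scale.* This is not general. In one lognormal scenario at ρ = 0.8 it matched ANCOVA (82% against 80%). For BMI, restricted to 30-40 at entry, an assumed uniform distribution with ρ 0.90-0.95 gave 76%, against 77-79% for ANCOVA.
- *A significant change in the butyrate arm only would be claimed as efficacy.* The article defines its outcomes as comparisons between the arms and ties no efficacy claim to a paired test.

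**Conclusion.** The point holds in a limited form. For each outcome the article plans an unadjusted test and an ANCOVA at the same threshold without saying which decides. It also leaves the covariates beyond baseline open and gives percentage change and within-arm tests no descriptive-only status.

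The cost is moderate. The error per outcome is about 6-9% if the better of the two between-group analyses is reported, and up to about 10% if percentage change is tested as well. About 9-10 points of power are lost for GLP-1 if the unadjusted change test is used at ρ = 0.5, and little at ρ = 0.9. These sizes rest on assumed correlations, CVs and distributions. They are per outcome and do not include multiplicity across the primary outcomes, which is a separate matter. The change should be made, because it costs almost nothing and restores the nominal 5% per outcome.

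**What to change.** Amend the Statistical analysis section as follows.

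1. Name one deciding analysis for each continuous outcome: ANCOVA of the end-of-study value on arm, baseline value and the randomisation strata (age group, sex), reporting the adjusted difference with its 95% CI. On the untransformed scale this equals the baseline-adjusted difference in change, so it still answers the question in the Outcomes section.
2. List before unblinding which outcomes are analysed on a log scale because skewness is expected.
3. For the three genes, analyse end-of-study delta-Ct adjusted for baseline delta-Ct and the strata, and back-transform the arm difference to a fold change. An end-on-baseline model cannot be applied directly to a fold change that already contains the baseline.
4. Remove the Kolmogorov-Smirnov gate and keep a rank-based test as a sensitivity analysis only.
5. Report percentage change and within-arm change descriptively, without P values.

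The cost is wording. No extra data or participants are needed, since baseline and strata are already recorded. The small downside is that transforms and covariates must be fixed before unblinding.

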### Adverse effects, safety, and data monitoring

SB supplementation at dosage of 600 mg/day is not known to have any side effect [11]. Two supervisors from a Data Monitoring Committee (DMC) will monitor the outcome of the RCT. The DMC is independent of the study organizers (sponsor and trial investigators).

Furthermore, the report of potential side effects will also be forwarded to the Ethics Committee of Ahvaz University of Medical Sciences.

## Discussion

Recent studies have revealed that microbiota-associated metabolites may play an imperative role in obesity and metabolic disturbances related to it [11, 12]. Butyrate action is linked to the activation of mitochondria and energy expenditure enhancement via activation of PGC-1α. PGC-1α is a transcriptional activator identified as a viable molecular target for dietary interventions [29]. PGC-1α regulates energy metabolism and fatty acid oxidation by expressing mitochondrial biogenesis and respiration genes by interacting with several transcription factors such as PPARα and UCP1 [30]. PPARα is also expressed in various tissues involved in fat oxidation in the heart, vascular, and endothelial cells and regulates the expression of genes involved in the transport and beta-oxidation of fatty acids in the mitochondria [31]. PPARα stimulates lipolysis and increases the uptake of fatty acids by increasing the expression of fat transporters and lipid metabolizing enzymes. Studies have also shown that the activated PPARα can improve glucose metabolism and weaken inflammatory processes [32, 33].

Uncoupling proteins (UCPs) are protein transporters in the mitochondrial membrane which separate the oxidative metabolism pathway from adenosine diphosphate (ADP) phosphorylation and adenosine triphosphate (ATP) synthesis via directing protons to the mitochondrial matrix to produce heat [34]. Therefore, UCPs are candidate genes for obesity and metabolic complications associated with obesity, and measuring the expression of UCPs is a method for assessing the oxidation of fatty acids [33, 35, 36]. On the other hand, activating genes related to UCPs have been identified as BAT activation markers. Increasing BAT activity is also vital for energy metabolism and is considered as a key factor that affects insulin sensitivity [37].

Based on several health benefits of Butyrate and the lack of adequate human studies, RCTs are required to evaluate the effects of SB supplementation on markers of metabolic pathway and anthropometric indices in the obese subjects. The strengths of this triple-blind randomized controlled clinical trial are the evaluation of the effects of SB supplementation and individualized hypo-caloric diet plan on obese subjects. We expect that the outcomes of this trial, whether positive or negative, will fill the gap in the literature and facilitate the development of multi-center clinical trials with a substantially larger sample size.

## Trial status

Recruitment for this trial has begun at June 2021 and is expected to be completed by November 2021 (now, it is underway).

## Data Availability

The datasets will be accessible to all principal investigators. Any participant identifying information will be removed from data dispersed to the research team to ensure confidentiality. The dataset generated during the current study will be available via the corresponding author upon reasonable request. The results and findings of the study will be released through publications in scientific literature and conference presentations. All those who involved in the design and implementation of this protocol will be author in the articles resulting from this research project.

